# Study Summary

| **Title** | A randomized, controlled, partially double-blinded, Phase 3, Multi-center trial to determine if Curosurf® reduces the duration of mechanical ventilation in infants 24+0 to 31+6 weeks gestational age |
| --- | --- |
| **Short Title** | Curosurf study |
| **Protocol Number** | Curosurf-01 |
| **Phase** | Phase 3 |
| **Methodology** | Randomized, partially double-blinded study using a 1:1 randomization, of ventilated infants to receive either Curosurf® or BLES® by endotracheal method. |
| **Study Duration** | This study is expected to last 30 months, including time for analysis. |
| **Study Center(s)** | Multi-center, multiple sites in Canada |
| **Objectives** | The objective of the study is to determine whether the duration of ventilation in babies who receive Curosurf® is less than those who receive BLES® |
| **Number of Subjects** | The projected enrollment is 88 patients. Enrollment is competitive. |
| **Diagnosis and Main Inclusion Criteria** | Infants born between 24+0 and 31+6 weeks GA, admitted to the study centers NICU’s, with RDS, requiring intubation and surfactant therapy. |
| **Study Product, Dose, Route, Regimen** | Infants will be randomized in a 1:1 manner, to receive either the study drug, Curosurf® or the control drug, BLES®. The treatment dose for Curosurf® is 2.5 ml/kg (200mg/kg) for the first dose and 1.25 ml/kg (100mg/kg) for repeat doses. For BLES® the recommended dose is 5 ml/kg. Either drug is given by syringe into the endotracheal tube by a Respiratory Therapist. |
| **Duration of administration** | The study drug or control drug will be given once all inclusion and no exclusion criteria have been met. In the days to follow according to the status of the infant, repeated doses may be indicated. |
| **Reference therapy** | The control group will receive BLES®. This licensed medication is routinely used in both study centers for the treatment of ventilated infants with a diagnosis of RDS. |
| **Statistical Methodology** | Analysis of the primary outcome will use logistic regression, with the treatment group as the main independent variable, and adjusting for the stratification variables, centre and gestational age category. Secondary analyses will include comparison of mortality rates by treatment group using a similar logistic regression model. |

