## Study Endpoints

**Primary Endpoint**

The primary efficacy endpoint is that the patient is alive and extubated at 48 hours post surfactant administration. We hypothesize that Curosurf® will increase the proportion of infants alive and extubated within 48 hours after surfactant therapy.

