# Statistical Plan

## 8.1 Sample Size Determination

Review of our data on duration of ventilation indicates that in 2010, 40% of patients meeting inclusion criteria were alive and extubated 48 hours after BLES®. We anticipate that the mean length of ventilation in the BLES® group will be similar or shorter in 2012. We therefore based our sample size calculation on the percentage of successful extubation within 48 hours in the BLES® group lying between 40% and 55%. Fixing the probability of type-I error at 5%, a sample of size of 44 per group will provide power in excess of 80% to detect an absolute difference of 30% in the percentage still intubated at 48 hours. (See Table)

| Percentage alive and extubated at 48 hrs | |  |  |
| --- | --- | --- | --- |
| BLES® group | **Detectable in Curosurf® group** | Risk difference | Relative risk reduction |
| 40% | **69.3%** | 29.3% | 0.488 |
| 45% | **73.9%** | 28.9% | 0.525 |
| 50% | **78.3%** | 28.3% | 0.566 |
| 55% | **82.3%** | 27.3% | 0.607 |

A recent RCT in a similar population found that 52% of infants who received Curosurf® were extubated by 48h compared to 22% of infants who received Survanta, an absolute reduction of 30% (15).

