## 8.2 Statistical Methods

Demographic and clinical characteristics of patients at baseline will be summarized by treatment group. Continuous variables will be summarized using mean, standard deviation, median, and interquartile range, as appropriate. Discrete variables will be summarized using frequency and percent. Analysis of the primary outcome will use logistic regression, with treatment group as the main independent variable, and adjusting for the stratification variables, centre and gestational age category. The intention to treat principle will be followed. Secondary analyses will include comparison of mortality rates by treatment group using a similar logistic regression model. Use of oxygen at 36 weeks will be analyzed similarly. Cox regression will be used to compare duration of ventilation by treatment group, adjusting for centre and gestational age category. Duration of oxygen support will be analyzed similarly. Durations for any patients who die while still on ventilation will be treated as censored values. Incidence of adverse events by treatment group will be summarized descriptively.

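### The Cox analysis that censors deaths on the ventilator gives a valid extubation hazard, but cannot by itself support a conclusion about duration of ventilation

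*Protocol*

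**What the plan says.** The Study Summary gives the trial's aim as to "determine whether the duration of ventilation in babies who receive Curosurf® is less than those who receive BLES" (the control product). The formal primary endpoint is different: "The primary efficacy endpoint is that the patient is alive and extubated at 48 hours post surfactant administration". Death before 48 hours is therefore a failure.

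For duration, Section 8.2 says: "Cox regression will be used to compare duration of ventilation by treatment group, adjusting for centre and gestational age category". It adds: "Duration of oxygen support will be analyzed similarly". On deaths the rule is explicit: "Durations for any patients who die while still on ventilation will be treated as censored values". Mortality has its own comparison: "Secondary analyses will include comparison of mortality rates by treatment group using a similar logistic regression model".

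The censoring rule is fixed in the protocol. It is not a detail left open for the statistical analysis plan.

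**The concern.** Death on the ventilator is not loss to follow-up, since it rules out later extubation. Censoring at death removes the infant from the risk set. The fitted ratio then compares how fast infants who are still alive and ventilated get extubated. It does not compare how many infants come off the ventilator alive, or how soon across everyone randomised.

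Read as a statement about duration, the censored ratio treats an infant who died as if extubation would have come at the rate of those still at risk. Infants who die ventilated are plausibly the sickest, so that reading is doubtful. The protocol also treats the same death in two ways: a failure in the primary endpoint, and a neutral removal in the duration analysis. If deaths were unequal, a report could call ventilation time similar although one arm had fewer infants extubated alive.

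**Working it through.** **1. The plan's own figure.** Section 8.1 says "Fixing the probability of type-I error at 5%, a sample of size of 44 per group will provide power in excess of 80" per cent for a 30-point difference. A two-proportion test (pooled variance, two-sided 5%, 44 per group) gives 81.9%, 83.1%, 85.2% and 88.0% for control rates of 40%, 45%, 50% and 55%. The figure reproduces and is not in dispute.

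**2. A case that can be done by hand.** Section 8.1 reports that "40% of patients meeting inclusion criteria were alive and extubated 48 hours after BLES". Take 40% extubated by day 2 (before deaths) with a constant hazard, the same in both arms: h = −ln(0.6)/2 = 0.255 per day. Assume 10% die ventilated in one arm and 20% in the other, unrelated to readiness for extubation. The death hazard is h·d/(1−d), which is 0.028 and 0.064 per day.

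- Cause-specific hazard ratio: h/h = 1.00.
- Ever extubated alive: 1−d, so 90% vs 80%.
- Extubated alive by 48 hours: (1−d)·[1−exp(−2h/(1−d))], so 39.0% vs 37.8%.
- Cumulative subdistribution hazard, −ln(1−incidence): at 48 hours 0.494 vs 0.474, ratio 0.96; at the end −ln(0.1) = 2.30 vs −ln(0.2) = 1.61, ratio 0.70.

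A single fitted subdistribution ratio averages between these, and simulation gives 0.81. The censored ratio of 1.00 is correct as an extubation hazard, but does not show the 10-point difference in infants leaving the ventilator alive.

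**3. Simulation over a range.** All death rates are assumed. There is no treatment effect on extubation in any row. A ratio above 1 means faster extubation in the second arm.

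| Ventilator deaths, first vs second arm | Who dies | Deaths censored | Deaths kept as never extubated |
|---|---|---|---|
| 10% vs 10% | either pattern below | about 1.0 | about 1.0 |
| 10% vs 20% | unrelated to readiness | 1.00 | 0.81 |
| 10% vs 20% | sickest 30% only | 1.13 | 0.85 |
| 10.5% vs 19% | graded severity (log-normal, SD 0.8) | 1.05 | 0.86 |
| 19% vs 10% | graded severity | 0.98 | 1.19 |

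With lower mortality the gap shrinks. At 4% vs 7.5% the pair is about 1.00 and 0.91; another run at 4% vs 7% gave 1.01 and 0.96.

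**4. Precision.** With 90% and 80% of 44 extubated there are about 40 and 35 events. SE(log HR) ≈ √(1/40 + 1/35) = 0.23, so a 95% interval spans a factor of exp(1.96 × 0.23) ≈ 1.6 either way. In 400 simulated trials per scenario at this size, the two methods were never significant in opposite directions.

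**5. Does the mortality comparison protect the reader?** By the formula in step 1, power at 44 per arm is about 26% for deaths of 10% vs 20% and about 46% for 10% vs 25%. An imbalance large enough to move the ratio would usually be non-significant.

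**The case against.** The strongest reply is that nothing is estimated wrongly. Censoring a competing event in a Cox model is the standard way to estimate a cause-specific hazard. When trials are simulated with a true extubation ratio of 1.3, the censored model returns 1.29 to 1.31. The lower figures come from a different estimand that mixes extubation with mortality. This stands. A reader might infer that the censored analysis is biased, or that the correct analysis reverses the sign. The documents do not support that: the two models answer different questions.

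The primary endpoint and the separate mortality analysis already count deaths, and reporting them next to an extubation hazard is a recognised approach. This stands in part, since step 5 shows the mortality test to be a weak safeguard.

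Duration is in the title and the Study Summary, but the primary objective and the sample size rest on the 48-hour endpoint. This stands: the analysis is secondary.

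A reader might also infer that the rule flatters Curosurf. The protocol gives no mortality rate for either product. Its Background cites a meta-analysis with higher survival on Curosurf, but against Survanta; the risks section calls the listed risks independent of surfactant type. If survival were better on Curosurf, censoring would work against it, as the last table row shows.

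Finally, the censoring sentence covers death while ventilated. What happens to an infant who dies on oxygen but off the ventilator is not stated, so extending the rule to that case is inference.

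**Conclusion.** The point holds in a limited form. The censored Cox model is valid for the extubation hazard, but cannot alone carry a conclusion about duration of ventilation. If ventilator deaths differ by arm, it can look neutral while fewer infants in one arm come off the ventilator alive, and this can happen in either direction.

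Under assumed deaths of about 10% vs 18–20%, the ratio is about 1.00–1.13 with deaths censored and 0.81–0.87 with deaths kept as never extubated. With few deaths the gap is small; with equal deaths it vanishes. These sizes rest on assumed mortality and on assumed links between severity and death. With a standard error near 0.23, gaps of this size lie within the noise of a single trial. The matter is the estimand and the reading of a secondary analysis. It does not touch the primary result, and it is a cheap improvement rather than a serious defect.

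**What to change.** In Section 8.2, replace the censoring sentence with wording to this effect:

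*Death on ventilation is a competing event for extubation. Cumulative incidence of extubation alive will be shown by arm and compared with a subdistribution-hazard model adjusted for the two stratification factors. Infants who die stay in the risk set to their potential end of follow-up, the date on which they would have reached 36 weeks GA. Statements about ventilation time rest on this analysis. The cause-specific Cox model and mortality are reported beside it.*

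For oxygen duration, treat death while on oxygen as a competing event in the same way.

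The cost is one extra standard model, with no new data: Appendix D already lists duration of first intubation, total support, oxygen days and mortality before discharge. The drawback is that a subdistribution ratio mixes extubation rate with mortality and may not be constant over time (0.96 falling to 0.70 in step 2). It should be read with the incidence curves and the cause-specific ratio. The choice should be fixed before deaths are seen by arm.

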# Background Information and Scientific Rationale

## Background Information

Evidence for the efficacy of either prophylactic (within the first 30 minutes after birth regardless of respiratory status) or selective (when signs of respiratory distress syndrome or RDS are present) administration of surfactant comes from meta-analyses, which demonstrate a consistent 30-50% reduction in the odds of neonatal death and air leaks (1). As the increase in survival is mainly observed among extremely low birth weight (ELBW) infants, the incidence of bronchopulmonary dysplasia (BPD) - the chronic lung disease that follows ventilator and O2 therapy for RDS - has not been significantly reduced. BPD, defined by the need for supplemental O2 at 36 weeks post menstrual age (PMA), increases the risk of mortality and pulmonary and neurodevelopmental morbidity among ELBW infants (2). Recent large RCTs have demonstrated that early nasal continuous positive airway pressure (nCPAP) with selective surfactant therapy was as effective at reducing BPD or death as intubation and prophylactic surfactant (3-5).

Currently, the two surfactants available in Canada are BLES® (Bovine Lipid Extract Surfactant) purified from bovine lung lavage and beractant (Survanta) extracted from minced bovine lungs. Most neonatal intensive care units (NICUs) use BLES®, for its observed faster onset of action. The recommended dose is 5 ml/kg, the highest for an animal-derived surfactant. Recent observations of severe airway obstruction (SAO) with desaturation and/or bradycardia with BLES® were reported in a cohort of premature infants, with an incidence of SAO of 31% in ELBW infants (6).

In Europe and the USA, the most widely used surfactant is poractant alfa (Curosurf®), a surfactant extracted from porcine minced lungs. Compared to BLES® and Survanta, Curosurf® contains a higher concentration of phospholipids (27, 25, and 76 mg/ml respectively). This accounts for the dramatic improvement usually observed immediately after its administration, which translates into a higher rate of extubation success (7-9). The treatment dose is 2.5 ml/kg (200mg/kg) for the first dose and 1.25 ml/kg (100mg/kg) for repeat doses if indicated. A recent meta-analysis confirms that Curosurf®, compared to Survanta, leads to higher survival, shorter duration of mechanical ventilation, less re-dosing (needing > 1 dose of surfactant) and shorter admissions to NICU (10).

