# Study Objectives

The objective of the study is to compare the efficacy of the 2 surfactants Curosurf® and BLES®, at facilitating extubation and reducing pulmonary morbidities and also to compare the adverse events during surfactant administration in very premature infants. We hypothesize that, compared to BLES®, Curosurf® will increase the proportion of infants alive and extubated within 48 hours after surfactant therapy.

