**Secondary objectives**

To compare the duration of respiratory support, extubation failure rates, need for additional surfactant doses, adverse events (during and following administration), survival and pulmonary morbidities during hospital admission between the two groups.

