**Secondary Endpoints**

The following endpoints will also be measured in this study:

- duration of respiratory support (respiratory support via an endotracheal tube and non-invasive respiratory support)
- duration of NICU stay
- extubation failure rates
- need for additional surfactant doses
- adverse events (during and following administration of surfactant)
- death before discharge
- incidence of pulmonary morbidities up to 36 weeks GA

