# Appendix D: Secondary Outcomes

1. Extubation failure (defined as in Appendix C )

2. Duration of first intubation (in hours/days)

3. Total duration of respiratory support (ventilator and nCPAP) and

Total number of days of oxygen requirement

4. Number of doses of surfactant received

5. Adverse events during or after administration of surfactant:

a) Severe airway obstruction, defined as sudden and severe desaturation < 80% with bradycardia (heart rate <100 bpm) with absence of visualization of chest movements with no response to increases in ventilator pressure or bagging for ≥3 minutes and requiring suctioning of surfactant or change of endotracheal tube (ETT)

b) Need for cardiopulmonary resuscitation

c) Pulmonary hemorrhage, defined as fresh blood in the ETT lumen associated with an increase in ventilation or oxygen requirements

d) Pulmonary air leaks (pneumothorax and/or pulmonary interstitial emphysema (PIE) on CXR)

6. Bronchopulmonary dysplasia, defined as oxygen or respiratory support requirement at 36 weeks corrected GA

7. Mortality prior to discharge

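### The arms are to be compared on adverse events around surfactant dosing, but Section 8.2 pre-specifies no between-arm estimate or interval for those events

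*Protocol*

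**What the plan says.** Section 2 (Study Objectives) includes in the overall aim "also to compare the adverse events during surfactant administration in very premature infants". The secondary objectives in the same section list, among the items to be compared, "adverse events (during and following administration), survival and pulmonary morbidities during hospital admission between the two groups". Section 4.2 repeats these adverse events as a secondary endpoint.

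Appendix D item 5 gives four events: severe airway obstruction, need for cardiopulmonary resuscitation, pulmonary hemorrhage and pulmonary air leaks. Severe airway obstruction has a detailed operational definition covering saturation, heart rate, chest movement, duration and the response needed.

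Section 1.1 gives the only background rate for any of these events, for BLES: "with an incidence of SAO of 31% in ELBW infants". Section 1.3 suggests that the smaller Curosurf volume may mean fewer complications from airway obstruction. It also says that the risks of surfactant, including air leak and pulmonary hemorrhage, do not depend on which surfactant is used.

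On analysis, Section 8.2 states: "Incidence of adverse events by treatment group will be summarized descriptively". Earlier in the same paragraph it says: "Discrete variables will be summarized using frequency and percent". For another secondary outcome it is more specific: "Secondary analyses will include comparison of mortality rates by treatment group using a similar logistic regression model". Oxygen use at 36 weeks is to be analysed in the same way, and durations of ventilation and of oxygen support get Cox regression.

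**The concern.** Descriptive tables are the usual and adequate treatment of general adverse events. These four events have a different standing: they are defined secondary outcomes, and the objectives promise a comparison between arms. A comparison needs a contrast and a statement of its uncertainty, and Section 8.2 names neither.

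With about 44 infants per arm, two percentages side by side can mislead in both directions. A difference that looks large may be compatible with none, and similar percentages may hide a material difference.

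If the contrast is not fixed beforehand, the effect measure and the counting unit can also be chosen after the results are seen. Section 7.2 allows up to three doses per infant, so a rate per dose and a rate per infant can differ.

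**Working it through.** **Inputs from the Protocol.** 88 infants randomised 1:1, so n = 44 per arm (Sections 4.1, 7.2 and 8.1). Severe airway obstruction on BLES: 31%, in ELBW infants only (Section 1.1). Enrolment runs from 24+0 to 31+6 weeks (Section 3), so applying 31% to everyone is an assumption.

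**Inputs assumed.** Curosurf rate 15%. A lower pair, 15% (BLES) and 7% (Curosurf), for infants at lower risk. Equal rates of 31% and of 10%. None of these comes from the Protocol, apart from the 31%.

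**The plan's own figure.** The Protocol gives no power or precision for adverse events. Its sample size for the primary endpoint reproduces with the usual two-proportion formula (pooled variance under the null, two-sided 5%, no continuity correction). For 40% against 70%, mean 55%:

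- z = [0.30 × √44 − 1.96 × √(2 × 0.55 × 0.45)] / √(0.40 × 0.60 + 0.70 × 0.30) = (1.990 − 1.379) / 0.671 = 0.911, so power = 81.9%.
- For BLES rates of 45%, 50% and 55% and a 30-point difference, power is 83.1%, 85.2% and 88.0%.

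This agrees with the stated power above 80%. It confirms 44 per arm as the working number but does not bear on the adverse-event question.

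**Precision of a risk difference at 44 per arm.** Difference = p(Curosurf) − p(BLES). Half-width = 1.96 × √[p1(1 − p1)/44 + p2(1 − p2)/44], without stratification.

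- 31% against 15%: √(0.2139/44 + 0.1275/44) = 0.0881 and 1.96 × 0.0881 = 0.173. Difference −16 points, 95% CI −33.3 to +1.3.
- 15% against 7%: √(0.1275/44 + 0.0651/44) = 0.0662 and 1.96 × 0.0662 = 0.130. Difference −8 points, 95% CI −21.0 to +5.0.
- Equal rates of 31%: half-width 19.3 points.
- Equal rates of 10%: half-width 12.5 points.

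**Check with a method suited to small counts.** Newcombe interval for 7/44 (Curosurf) against 14/44 (BLES): difference −15.9 points, 95% CI −32.7 to +2.0. The Wald approximation is close enough for this purpose.

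**Expected event counts.** At 31% and 15%: 44 × 0.31 + 44 × 0.15 = 13.6 + 6.6, about 20 infants with an event. At 15% and 7%: 6.6 + 3.1, about 10. Two gestational-age strata can be supported with such counts. Crossing them with centre would leave very few events per cell.

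**The case against.** The strongest reply is that Section 8.2 is a high-level summary. Its sentence on adverse events does not forbid an interval, and the effect measure, interval method and counting rule are normal content for an SAP. That is fair as to detail. The Protocol is not silent, however: it states a method, and that method stops short of the comparison promised in Section 2. An SAP that followed Section 8.2 literally would carry the mismatch forward.

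The sentence on frequency and percent follows directly on the baseline characteristics, so reading it as a limit on adverse-event reporting is an inference. The point does not depend on it.

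Three stronger readings are tempting and are not supported.

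- A reader might infer that the trial yields no estimate at all for its safety question. It will report incidence per arm, and anyone can derive a crude difference and interval from the counts. What is absent is a pre-specified contrast.
- A reader might infer that a benefit is expected on all four events. Section 1.3 expects it only for complications of airway obstruction and calls air leak and pulmonary hemorrhage independent of surfactant type.
- A reader might infer that adverse events alone were left without a model. Extubation failure, additional doses and length of NICU stay also have no named between-arm analysis in Section 8.2.

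It can also be said that a trial of 88 infants has little power for such events. That is a good reason not to test. It is no reason to omit an interval, which is what shows the reader how little the data can say.

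**Conclusion.** The mismatch is real and narrow. The Protocol promises a between-arm comparison of adverse events around dosing, defines four such events, and then plans only per-arm description. The case is strongest for severe airway obstruction, which has both a background rate and a directional expectation.

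The size is illustrative. If the ELBW rate of 31% held for all BLES infants and Curosurf had 15%, the interval would run from about −33 to +1 points. At lower or equal rates the half-widths lie between about 12.5 and 19 points. All rates other than the 31% are assumed, and the intervals are unstratified.

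The primary endpoint, the sample size and the data to be collected are unaffected.

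**What to change.** Add to Section 8.2: for each Appendix D item 5 event, severe airway obstruction first, the risk difference (Curosurf minus BLES) per randomised infant over all study doses will be reported with a 95% CI stratified by gestational-age category (for example Miettinen-Nurminen or Newcombe). State that these results are supportive and carry no formal test. Give the reason for leaving centre out of the stratification: event counts will be sparse. Keep descriptive reporting for all other adverse events.

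The cost is a short addition to the text and four more intervals to report. Those intervals will be wide, and the report should say so.
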